## Abstract

**Background:**

Stigma is prominent in the lives of autistic individuals and their families and contributes significantly to the challenges faced by families raising an autistic child. Parents and carers can feel blamed for their child’s behaviour, feel socially excluded and isolated and suffer from low self-esteem and poor psychological well-being. This increases the risk of experiencing self-stigma which further exacerbates these and other negative consequences. Therefore, there is a need for interventions that help parents/family carers cope with autism-related stigma as well as prevent the internalisation of stigma.

**Objectives:**

The primary objective of this study is to assess the feasibility and acceptability of a stigma support intervention for parents and carers of autistic children titled ‘Stigma of Living as an Autism Carer (SOLACE)’. The secondary objective is to explore the preliminary impact of the intervention on the mental health of the parents and carers.

**Methods:**

A pilot randomised controlled trial feasibility study will be implemented. A group receiving the SOLACE stigma support intervention (*n* = 12) will be compared against a control group not receiving any additional intervention (*n* = 12). Family carers of autistic children up to the age of 10, who have been recently diagnosed or are currently undergoing diagnosis, will be recruited for the study. Participants will be randomly allocated to the intervention or control group and will take part in eight weekly group-based sessions designed to improve the well-being of the parents primarily through increasing their resilience to stigma. Feasibility will be determined by recruitment and retention rates and a qualitative focus group evaluating the acceptability of the intervention and outcome measures. The primary outcome of interest is psychological well-being, and depending on the normality of distribution, independent samples *T* tests will be used to compare the outcome scores between the two groups and dependent samples *T* tests for differences within the group. Other outcomes of interest are stigma, self-stigma, self-esteem, self-blame, social isolation, self-compassion and perceived responsibility and control.

**Discussion:**

Results from the feasibility randomised controlled trial will be used to refine the study protocol and inform the design of an intervention for future use in a larger, powered trial. SOLACE could potentially improve the psychological well-being of parents/family carers of autistic children through increased resistance to stigma.

**Trial registration:**

ISRCTN Registry number ISRCTN61093625 (October 13, 2017).

**Electronic supplementary material:**

The online version of this article (10.1186/s40814-019-0406-9) contains supplementary material, which is available to authorized users.

## Background

Autism Spectrum Condition (ASC) is a neurodevelopmental condition characterised by diagnostic professionals as impacting upon social interactions, verbal and nonverbal communication, and a narrow spectrum of interests and behaviours [1]. About 1 in 68 children is reportedly on the autism spectrum according to estimates from CDC’s Autism and Developmental Disabilities Monitoring Network [2].

Parents of autistic children report higher parenting stress and lower psychological well-being than the general population [3] and compared to parents of children with other disabilities [4, 5]. The socially challenging behaviours associated with autism contribute to the difficulty of raising an autistic child [6] but so does the public response to this behaviour. Parents in numerous studies report finding the stigma surrounding autism particularly challenging [7–9]. Parents report feeling blamed for their child’s atypical behaviour [10, 11] which subsequently undermines their confidence in their parenting abilities and negatively affects their self-esteem [12, 13]. Negative reactions and attitudes from others also lead families to feel socially isolated [14] and socially excluded [15].

Stigma is prominent in the lives of families with an autistic family member, with up to 95% of families reporting to experience some form of stigma [15–17]. Ali et al. carried out a systematic review of 20 studies to assess the impact of stigma on the well-being of carers and parents of children with intellectual disabilities, including autism [18]. Their results demonstrated that stigma affects the psychological well-being in parents and leads to an increase of parental stress and increased caregiver burden. A recent systematic review carried out by Papadopoulos et al. [19] explored the relationship between autism-related stigma and the mental health of informal caregivers. The review, which assessed nine studies with diverse study designs from across varied socio-cultural settings, consistently found that stigma has a harmful impact on the mental health of caregivers. For example, autism-related stigma was found to be directly related to depression [12, 20], anxiety [21] and psychological distress [22].

A relatively new concept in the autism stigma literature is that of ‘self-stigma’ among parents and family carers. Self-stigma among parents/carers has been defined as the phenomenon by which the public’s negative stereotypes towards both autistic people and, crucially, their family carers, subsequently becomes accepted by parents/carers and incorporated within their own psychological identity [23]. Interviews with parents of autistic children in studies from Cashin [24] and Woodgate, Ateah and Secco [14] have demonstrated how parents of autistic children experience changes to their sense of self and their identity. Self-stigma among parents/carers has also been referred to as ‘affiliate stigma’ [25]. Ntswane and Van Rhyn [26] explored affiliate stigma in a group of South-African mothers of children with intellectual disabilities including autism and found that mothers feel shame, anger, fear, frustration and disappointment. Affiliate stigma has been linked to reduced self-esteem, reduced hope and self-efficacy, reduced quality of life and social avoidance [27, 28].

Parents and carers are recognised as crucial for the well-being of children with disabilities [29, 30]. Given the evidence that connects stigma with the mental health and well-being of parents and carers [19], we theorise that increasing the resilience to stigma will have a positive impact on their well-being and subsequently their caregiving abilities. The development of interventions to reduce self-stigma is still a relatively new area of research. Furthermore, early interventions focused on new carers could be particularly important since they may be more vulnerable to self-blame during the early stages of diagnosis and, as such, to affiliate stigma. New carers are more vulnerable to the misconceptions associated with autism given this may be the first time they have ever encountered autism [19]. Therefore, they may be more prone to misconceptions, myths and negative stereotypes [31].

To our knowledge, there are currently no intervention programs available that help carers of autistic children protect against and cope with the stigma they experience. The aim of the current study is to address this unmet need of carers of autistic children and to contribute to this important gap in the literature. Because there are currently no interventions available, it is unknown what will be effective, acceptable and achievable with regards to the logistics and practicalities of such intervention. It is, therefore, necessary to carry out a feasibility study to assess the feasibility and acceptability of the intervention for a future larger trial. This proposal describes the protocol of a feasibility study designed to evaluate the feasibility and acceptability of a brief psycho-social support intervention, titled ‘Stigma of Living as an Autism Carer (SOLACE)’, for parents/carers of young autistic children. The secondary objective of the study is to evaluate the preliminary results regarding the impact this intervention produced on mental health.

## Methods

### Design

This study is a feasibility study of a parallel randomised controlled trial (RCT) that compares changes in outcomes of interest among parents/carers allocated to the SOLACE experimental group against parents/carers allocated to a control group (no intervention). Standard Protocol Items: Recommendations for Interventional Trials (SPIRIT) checklist was used to structure and develop this protocol.

### Study setting

The study is based in the county of Bedfordshire (UK). Parents and carers will be recruited with help from Autism Bedfordshire, the largest autism charity in the county, and the Luton Borough Council Special Needs team by advertisements in their newsletter, their website and social media channels. The study will be advertised on the University Institute of Health Research’s website and social media channels as well as on the researcher and supervisors’ personal social media accounts. Parents and carers who are interested in taking part or finding out more information are invited to access the URL link to an online information sheet or can contact the research team directly. Digital informed consent will be sought before directing the participants to the baseline assessment.

### Study population and eligibility criteria

This study targets parents and carers of autistic children up to the age of 10 years who have been diagnosed within the past 12 months or are currently undergoing assessment. The participant inclusion criteria are the following: parents or carers aged 18 years or older who care for an autistic child aged up to 10 years and who reside within the county of Bedfordshire. Participants must be able to speak and understand English and are required to have access to the internet or a device able to conduct video-conferencing (e.g. mobile, tablet, PC with a camera and microphone). Individuals who do not fully meet the above criteria are excluded. Our goal is to recruit participants from Bedfordshire; however, if we are unable to recruit a sufficient number of participants from this area, participants from neighbouring counties may also need to be included.

### Sample size

As this is a feasibility study, it is not powered to determine statistical significance. The target recruitment for this feasibility trial is 24 (12 per group). This number is deemed appropriate for the study aims and consistent with recommendations for behavioural group intervention with this population [32].

### Randomisation and blinding

After completing the baseline questionnaire, all participants eligible to take part will be stratified based on gender and frequency of use of support groups (ranging from 0 (never) to 4 (often)) to minimise imbalance between the two groups. The participants will be randomised by an independent researcher via computer generated allocation using JavaScript’s Math functions [33] to either the SOLACE intervention or to the control group. Double-blinding of group allocation is not practically possible since the intervention will be facilitated by the researchers. Figure S1 illustrates the recruitment process and can be found in Additional file 1.

### Intervention: SOLACE

The intervention comprises of eight sessions and include theory, group discussions, short video clips, exercises and examples of parents/carers’ experiences. The intervention will be facilitated by the first author with the support of a voluntary assistant facilitator who will be recruited from the university’s Masters in Public Health course. During the intervention period, a ‘secret’ Facebook group, which only the experimental group participants will have access to, will be used to support the intervention and to boost retention rates. This will be administered and moderated by the lead facilitator. To further boost retention rates, weekly Facebook private messaging reminders will be sent to the experimental group participants.

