### Statistical analysis

Statistical analysis (using IBM SPSS v23 software) of the quantitative outcome measurements will be conducted following tool analytical guidance. Within group comparisons of the outcomes, measures will be made as well as between groups comparisons to examine preliminary effectiveness.

Kolmogorov–Smirnov tests will be initially conducted to establish the normality of the data. Depending on the normality of distribution, independent samples *T* tests, Mann–Whitney *U* tests and/or chi-square tests will be used to compare the outcome measures between the two groups. To assess potential within-group differences, dependent *T* tests (for normal distribution) or Wilcoxon signed-rank tests (for non-normal distribution) will be used. Individual and group-level descriptive analyses of both the frequency and/or central distribution (medians, means, standard deviation, range) of independent and dependent variables will also be conducted. Standard effect sizes of the primary outcome measure will be calculated (Cohen’s *α*) with confidence intervals to provide an initial estimate for sample size calculation for a future main RCT.

Furthermore, quantitative data will be descriptively analysed to assess rates and patterns of recruitment, follow-up and retention rates, and willingness of randomisation. The distribution of missing data within each measure will help to establish the acceptability of measures. Missing data will also be described via frequencies and cross tabulations against background characteristics to further assess the acceptability of the measurement tools.

Qualitative data will be thematically analysed using Nvivo (v11). This will involve in-depth familiarisation with the focus group data, systematic identification of codes to form a coding frame, indexing the data according to the coding frame to identify common themes and interpreting the findings in the context of other research [47].

The Consolidated Standard of Reporting Trials (CONSORT) extension to pilot trials will be followed for reporting the trial.

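### The effect-size interval meant to seed the main-trial sample size ignores clustering in the group-delivered SOLACE arm

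*Protocol article*

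**What the plan says.** On delivery, the abstract (Methods) says that participants "will take part in eight weekly group-based sessions". The section Intervention: SOLACE says "The intervention will be facilitated by the first author with the support of a voluntary assistant facilitator", and adds a closed Facebook group "which only the experimental group participants will have access to". The Content section and Table 1 make mutual support, joint tasks and a sense of belonging part of how the programme is meant to work. The Control group section leaves controls to their usual lives, with no group contact.

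On allocation, the unit is the person: "The participants will be randomised by an independent researcher via computer generated allocation" (Randomisation and blinding). On size, "The target recruitment for this feasibility trial is 24 (12 per group" and "As this is a feasibility study, it is not powered to determine statistical significance" (Sample size).

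On analysis, the Statistical analysis section names independent-samples t, Mann–Whitney or chi-square tests between arms. It adds a standardised effect size for the primary outcome "with confidence intervals to provide an initial estimate for sample size calculation for a future main RCT". No group, facilitator or design-effect term appears. The Discussion goes further and presents the study as a reliable guide to the sample size of the effectiveness trial, while allowing that conclusions on effectiveness are preliminary.

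**The concern.** People who share eight discussion sessions, an online group and a facilitator tend to have correlated outcomes, and here shared influence is an intended mechanism. Clustering exists in one arm only, so the design is partially nested. The planned tests and interval treat all 24 people as independent.

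If there is only one SOLACE group, its particular chemistry and facilitator cannot be separated from the effect of the programme. The point estimate absorbs that group's own effect, in either direction, and the interval carries no allowance for it. What is at stake is less the pilot's own decision than the next trial: the effect size and interval are explicitly meant to be carried forward, and an individual-level variance carried forward unadjusted understates the N that a group-delivered trial needs.

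**Working it through.** **Inputs from the documents.** N = 24 as 12 + 12 (Sample size); group delivery, one Facebook group and one lead facilitator in the SOLACE arm; ungrouped controls; independence-based analysis. The target of 24 is not a power calculation: no alpha, power, effect size or SD is given, so there is no planned figure to reproduce, and it is not in dispute.

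**Inference.** The number of SOLACE groups is not stated. One group of m = 12 is implied by 12 per arm, a single session series, one Facebook group, one lead facilitator and one week-9 focus group.

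**Assumptions.** ICC 0.01, 0.05 and 0.10, as the documents give none. For main-trial N: standardised difference d = 0.5, two-sided 5%, 80% power, groups of 12.

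**Formulas.**
- SOLACE-arm design effect: DE = 1 + (m − 1) × ICC = 1 + 11 × ICC.
- Variance factor for the difference between equal arms: V = (DE + 1)/2. The SE multiplier is √V.
- Proportion by which the unadjusted interval is too narrow: 1 − 1/√V.
- Required rise in N: V − 1. Shortfall of an unadjusted N: 1 − 1/V.
- Main-trial n per arm: (1.96 + 0.84)² × (DE + 1)/d².

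| | ICC 0.01 | ICC 0.05 | ICC 0.10 |
|---|---|---|---|
| DE | 1.11 | 1.55 | 2.10 |
| V | 1.055 | 1.275 | 1.55 |
| SE multiplier | 1.03 | 1.13 | 1.25 |
| Interval too narrow by about | 3% | 11% | 20% |
| Simulated coverage of nominal 95% interval | 94.4% | 91.7% | 88.1% |
| Required rise in N | 5.5% | 27.5% | 55% |
| Shortfall of unadjusted N | 5% | 22% | 35% |
| Main-trial total N (126 under independence) | 134 | 162 | 196 |
| Power if 126 is kept | 78% | 70% | 62% |

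Coverage comes from 200,000 simulated pilots per ICC, using the t-based interval on 22 degrees of freedom. With no clustering it was 95.0%. At ICC 0.05 the true SE was 0.460 SD against an average model SE of 0.398 SD.

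**If there were two groups of 6.** DE = 1 + 5 × ICC gives SE multipliers of 1.06 at ICC 0.05 and 1.12 at 0.10: smaller, but in the same direction. The facilitator would still be confounded with treatment.

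**Two carers of one child.** Eligibility is set per carer ("parents or carers aged 18 years or older who care for an autistic child aged up to 10 years"), so pairs are conceivable. Take k = 4 pairs with within-pair correlation r = 0.5. If every pair is in one arm, the variance of the difference is (24 + 2kr)/144 = 28/144 against 24/144, so the true SE is 1.08 times the independence SE. If every pair is split, it is 20/144, or 0.91 times. Under individual random allocation the two roughly cancel: simulated coverage was 95.0% at r = 0.3 and 94.9% at r = 0.5.

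**The case against.** The strongest reply is that this is a feasibility study. Its objective and continuation criteria concern feasibility and acceptability, it disclaims power, and it calls its effectiveness findings preliminary. With d near 0 the unadjusted 95% interval is already about ±0.85 SD (2.07 × √(2/12)), so no one should size a trial tightly from it. With one group no model can recover the missing variance, so no better analysis of these data is being passed over. All of this stands, and it limits the severity. It does not answer the point, because the protocol itself assigns the effect size and interval to main-trial sizing, and its caveat concerns small numbers, not clustering.

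Three stronger readings are tempting but not supported.
- A reader might infer that the main trial will be too small. No main-trial N exists yet. It falls short only if the later calculation omits a design effect, and the protocol does not say either way.
- A reader might take the 27.5% and 55% as shortfalls. They are required increases; the corresponding shortfalls are about 22% and 35%.
- A reader might infer that enrolling both parents also makes the interval too narrow. Under individual randomisation the net effect is about nil. What remains is possible contamination if a pair is split across arms. A rule on this may sit in the full protocol, so its absence from a condensed article is not itself a fault.

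**Conclusion.** The point holds in a limited form. The protocol commits to an independence-based interval for a group-delivered arm, carries it into main-trial sizing and describes the outcome as reliable without mentioning clustering. That interval omits between-group variance and is too narrow whenever the ICC is above 0. The size depends on an assumed ICC and on an inferred single group of 12: negligible at 0.01, and material from about 0.05, where coverage is about 92% and an unadjusted main-trial N would be about 22% too small. The feasibility objective and the target of 24 are unaffected. It is worth correcting because the error would pass into the next trial and the correction is cheap.

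**What to change.** - **Statistical analysis:** state that the effect size and its interval are descriptive, conditional on this SOLACE group and facilitator, and exclude between-group variance.
- **Statistical analysis:** state that main-trial sizing will multiply the SOLACE-arm variance by 1 + (m − 1) × ICC over a stated range of externally sourced ICCs, for example 0.01 to 0.10.
- **Discussion:** remove the word *reliable* from the claim about the future sample size.
- **Separate minor point:** to avoid contamination between carers of one child, enrol one carer per child or randomise by household. Household randomisation always puts a pair in the same arm, so the analysis must then allow for the pairing.

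The cost is a few sentences and no new data. The downside is a larger, less favourable main-trial figure, shown as a range. A one-carer rule may also lose a few second carers.

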### Control group

Participants allocated to the control group will be asked to continue with their normal day to day life as usual. Measures will be taken again post-intervention period (week 8) and 6 weeks post intervention (week 14) to describe potential preliminary differences between the control and intervention group. After the study period, an information pack including useful information and activities that were part of SOLACE will be provided to this group.

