### Outcome measures

Continuation criteria will be used to assess if further evaluation of this intervention is justified, through a formal RCT. The criteria for continuation will be based around feasibility and acceptability. A mix of quantitative and qualitative evaluation processes will be used to evaluate the feasibility of the intervention.

The outcome measures to assess feasibility and acceptability are the following:Recruitment rate, including willingness to be randomised.Drop-out rates including reasons will be recorded to help determine the acceptability of the intervention to participants.Missing data will be descriptively analysed in order to evaluate the acceptability of the data collection measures and procedures.Incidence of adverse events will be recorded that may arise during the intervention period.To evaluate the acceptability of SOLACE and the outcome measures, participants from the intervention group will be invited for a qualitative focus group discussion in week 9. The focus group interview will be audio-recorded for analysis. A topic list will be used to evaluate the intervention content, structure, format and mode of delivery. Positive quality feedback of participants regarding their experience of undertaking SOLACE should indicate whether a larger trial may be feasible.

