### Harms

The intervention is considered safe and there is no evidence to suggest that the planned intervention will be reasonably likely to cause any harm to participants. It is anticipated that the benefits of the study will be greater than any possible risk. Participants will be told that in the event that they do feel distress, they can withdraw from the study at any time. In such cases, we will offer participants the opportunity to debrief with the facilitator, as well as a list of caregiver mental health resources (including services across the county and relevant online support groups). Likewise, it is unlikely that participants will experience any harm during the focus group interview given that the focus will primarily regard the feasibility, practicality and acceptability of the intervention. It is ensured that all questions and probes used are phrased sensitively. Any adverse events that do occur will be recorded and reported when necessary. A protocol and record log for adverse events will be utilised.

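### Measures meant to boost retention are directed to the SOLACE arm only, so control-arm and pooled retention, and the comparison between arms, are open to differential attrition

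*Protocol article*

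**What the plan says.** All references are to the protocol article.

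- **Intervention: SOLACE.** During the intervention period there is a closed Facebook group, "which only the experimental group participants will have access to, will be used to support the intervention and to boost retention rates". The same section adds: "To further boost retention rates, weekly Facebook private messaging reminders will be sent to the experimental group participants".
- **Control group.** "Participants allocated to the control group will be asked to continue with their normal day to day life as usual". Measures are repeated at weeks 8 and 14. The only other item named for controls comes late: "After the study period, an information pack including useful information and activities that were part of SOLACE will be provided to this group". It is not described as an aid to retention.
- **Abstract, Methods.** "Feasibility will be determined by recruitment and retention rates and a qualitative focus group".
- **Outcome measures.** "Drop-out rates including reasons will be recorded to help determine the acceptability of the intervention to participants".
- **Statistical analysis.** Follow-up and retention rates are to be described. Outcomes are compared between arms by t test, Mann–Whitney or chi-square test. A standardised effect size for the primary outcome measure is to serve as a first estimate for sizing a main trial.

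**The concern.** Retention is one of the things this pilot exists to measure. As written, it is measured with weekly personal contact in one arm and no described contact in the other. Two uses of the data are exposed.

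The first is the retention figure itself. If a later trial again uses a control arm without intervention, its planners will need to know how many controls return questionnaires. Here that rate would come from the arm with no described support. A rate pooled over both arms would mix two levels of effort.

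The second is the outcome comparison. The people who return questionnaires at weeks 8 and 14 supply both the between-arm tests and the effect size passed to the main trial. If the arms lose different proportions, and those lost differ in well-being from those who stay, the completers are no longer comparable.

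The wording also leaves open what drop-out means. A SOLACE participant can stop the sessions, stop the questionnaires, or both. A control can only stop the questionnaires. The article does not say which of these the drop-out rate counts.

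**Working it through.** The plan has no figure of its own to reproduce: it states no expected drop-out, and the target of 24 (12 + 12) has no attrition allowance behind it. What follows is an illustration under assumed rates.

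**Inputs**
- From Sample size: n = 12 per arm.
- Assumed: drop-out d_S = 10% on SOLACE; d_C = 10% to 40% on control.
- Assumed: in each arm drop-outs have a mean k SD away from completers, with k = 0.5 to 1.0.
- Assumed: only completers are analysed. The article does not state its analysis set.

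**Step 1: completers and pooled rate.** Expected completers are 12 × (1 − d).
- SOLACE: 12 × 0.90 = 10.8.
- Control at 30% drop-out: 12 × 0.70 = 8.4.
- Pooled retention: (10.8 + 8.4) / 24 = 80%, which describes neither the 90% arm nor the 70% arm.

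**Step 2: chance of a visible gap.** The probability that controls lose at least three more people than SOLACE is the sum of Bin(i; 12, d_S) × Bin(j; 12, d_C) over all i, j with j − i ≥ 3.

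| d_S | d_C | Expected completers | Probability |
|---|---|---|---|
| 10% | 10% | 10.8 v 10.8 | 4% |
| 10% | 20% | 10.8 v 9.6 | 22% |
| 10% | 30% | 10.8 v 8.4 | 48% |
| 10% | 40% | 10.8 v 7.2 | 71% |

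**Step 3: shift in the outcome comparison.** The mean of everyone randomised to an arm is (1 − d) × completer mean + d × drop-out mean. If drop-outs lie k SD from completers, the completer mean is off by k × d. The between-arm difference among completers is therefore off by k × (d_C − d_S) in size.
- k = 0.5, 10% v 30%: 0.5 × 0.20 = 0.10 SD.
- k = 1.0, 10% v 30%: 1.0 × 0.20 = 0.20 SD.

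The sign depends on the assumptions. If drop-outs are worse off and controls lose more, the control completers look too well and the shift works against SOLACE. If SOLACE loses more, it reverses.

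**Step 4: scale.** With 10.8 and 8.4 completers, the standard error of the difference is √(1/10.8 + 1/8.4) = 0.46 SD, so the shift is about 0.2 to 0.4 of one standard error. Arm-level rates are also imprecise: 3 drop-outs of 12 has an exact 95% interval of 5% to 57%.

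**The case against.** The strongest reply is that the section describes how the intervention is delivered. The Facebook group also supports SOLACE, and a weekly message fits eight weekly sessions better than two questionnaires. Controls have no sessions to be reminded of. This stands in part: the prompts plausibly serve attendance, and drop-out from SOLACE with its reminders is a fair measure of acceptability of SOLACE so delivered. It does not help the control-arm rate, a pooled rate or the between-arm comparison. Retention is also the only purpose stated for the messages.

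A second reply is that a condensed article need not list questionnaire reminders, and none are described for either arm. That is fair, and a fuller document may provide them equally. It therefore cannot be asserted that controls will receive no reminder. But on retention measures the text is not merely silent: it names the experimental arm as recipient.

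Third, CONSORT reporting for pilot trials is promised, and drop-out and missing data are listed as separate outcomes. This helps, but does not explicitly separate stopping sessions from loss to follow-up.

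A reader might also infer from Harms, where distressed participants are told "they can withdraw from the study at any time", that anyone who stops sessions loses their week 8 and week 14 data. The section does not say so. It restates the right to withdraw and offers a debrief, and says nothing on whether questionnaires continue.

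**Conclusion.** The point holds as a moderate design weakness. Retention-directed effort is unequal by the article's own wording, and it bears on a feasibility criterion. The control-arm rate, any pooled rate and the between-arm comparison are affected; the SOLACE rate is not, provided it is read as retention with reminders.

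A reader might go further and conclude that the comparison will be biased. The documents do not support that. Differential loss is a risk: reminders may hold the SOLACE arm, while the burden of eight sessions may raise its drop-out. Bias also needs missingness that is related to outcome. The 0.10 to 0.20 SD is an illustration resting on assumed drop-out of 10% v 30%, an assumed 0.5 to 1.0 SD difference and an assumed completer analysis. It is smaller than the sampling error of a trial this size, which claims no power and treats impact on mental health as a secondary objective. The case for change rests mainly on what the pilot can report about retention, and on how little the change costs.

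**What to change.** 1. Send the same neutral questionnaire reminders to both arms at weeks 8 and 14, by the same channel, in the same number and at the same times.
2. Keep session-attendance prompts and the Facebook group as components of SOLACE, and describe them as such.
3. Report two quantities separately: session attendance and discontinuation (SOLACE arm only), and questionnaire completion at weeks 8 and 14 (by arm, not only pooled).
4. State that participants who stop attending sessions are still invited to complete both questionnaires unless they withdraw from follow-up.

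If equal questionnaire reminders already exist in a fuller document, one sentence saying so would replace item 1.

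The cost is a few automated messages to 12 controls and some rewording. The downside is slightly more contact with controls than continuing entirely as usual.
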